## Abstract

**Background:**

Although older adults with Mild Cognitive Impairment (MCI) face an increased risk of dementia, accumulating evidence has revealed that their cognitive functions could revert to normal levels with effective interventions. Exercise, particularly a combination of physical and cognitive training delivered in the form of an exergame, has shown promising effects in improving cognitive function of older adults with MCI. Nonetheless, previous research often prescribed center-based, moderate to vigorous intensity exercise, posing potential risks to older adults with physical or medical conditions as well as limiting accessibility for those with schedule or transportation constraints. Therefore, this study aims to evaluate the effects of home-based, low-intensity, combined physical-cognitive exercise in the form of an exergame, on cognitive function in individuals with MCI and to further investigate potential biomarkers linking the effectiveness of the exercise program to cognitive alterations.

**Methods:**

Sixty-four older adults with MCI will be enrolled and randomly allocated to either the exercise group or the control group. The exercise group will engage in a low-intensity, combined physical-cognitive exercise through an exergame, with a 50-minute session, 3 times per week for 12 consecutive weeks. The control group will not receive any intervention. Primary outcome measures will be cognitive performance (global cognition, executive function, memory, and attention), and secondary outcome measures will be plasma biomarkers and physical performance. All assessments will be administered at baseline and after a 12-week intervention.

**Discussion:**

The findings of this study might provide valuable insights into an effective and practical intervention program aimed at improving cognitive function of older adults with MCI. The low-intensity, home-based exergaming could have considerable clinical implications, as it has the potential to enhance accessibility for individuals who are unable to engage in high-intensity exercise or attend center-based exercise programs.

**Trial registration:**

ClinicalTrials.gov identifier: NCT06201533, Registered January 11, 2024.

## Background

With the world’s aging population, dementia, particularly Alzheimer’s disease (AD) has become a global pandemic. It is estimated that the number of people with dementia worldwide will reach 74.7 million in 2030 and 139 million in 2050 [1, 2]. Dementia is preceded by a preclinical phase, a syndrome called Mild Cognitive Impairment (MCI). Older adults with MCI are approximately 10 times more likely to develop dementia compared to cognitively intact older adults [3]. However, MCI is a potentially reversible condition, several individuals with MCI could revert to normal levels of cognition [4]. Therefore, interventions that could prevent cognitive deterioration and/or improve cognitive function in this population would significantly decrease the incidence of dementia.

Non-pharmacological intervention particularly exercise has shown promise in MCI management. Accumulating evidence has demonstrated that exercise could enhance cognitive function, reduce the risk of dementia, and improve physical performance and general quality of life in individuals with cognitive impairment [5–8]. The beneficial effects of exercise on cognition have been demonstrated for both global cognitive function and specific cognitive domains particularly memory, attention, and executive function in individuals with MCI [9, 10]. Among several types of exercise, a systematic review and meta-analysis revealed that the most profound effects are observed in combined physical-cognitive exercise [6]. Previous research has shown that individuals with MCI demonstrate greater improvement in cognitive function (e.g., learning and memory), hippocampal BDNF, and physical functioning when engaging in combined physical-cognitive training compared to either cognitive or physical training alone [11, 12]. The explanation for this phenomenon is that as each intervention is associated with different mechanisms, the neuroplasticity and synaptic integrity are boosted when the two interventions are combined [13].

With current technologies, simultaneous physical and cognitive exercise can be delivered in the form of an exergame, an exercise that involves moving the body to interact with the game. Exergames specifically designed for older adults have been proven to be safe, easy to use, and enjoyable, which in turn results in a high adherence rate [14, 15]. Exercise adherence has an important contribution to the success of an intervention. The effectiveness of exercise depends not only on the exercise program itself but also on the individual’s engagement. The meta-analysis study findings suggest that improvements in cognitive function were greater in samples where better adherence to the exercise training was reported, for both participants with AD and those at risk of AD [16]. Several studies demonstrated that exergames improve physical functions (e.g., balance, mobility, physical fitness, and gait) and cognitive function (e.g., executive functions, memory, and processing speed) among healthy older adults, older adults with metabolic syndrome, MCI, and dementia [14, 15, 17, 18].

Recently, research has expanded beyond investigating the impact of exercise on cognitive function to determining the underlying mechanisms by which exercise affects cognitive function in individuals with MCI. One of the most consistently observed effects of exercise is an increase in the level of plasma brain-derived neurotrophic factor (BDNF). Previous research suggested that exercise enhances cognitive performance, likely through the upregulation of BDNF in circulation [5, 19–22]. Additionally, several studies have examined the influence of moderate to vigorous exercise on inflammatory biomarkers, especially pro-inflammatory cytokines such as interleukin 6 (IL-6), interleukin 1β (IL-1β), tumor necrosis factor-alpha (TNF-α), and C-reactive protein (CRP) [5, 23]. For example, a previous study found that engaging in physical exercise enhances cognitive performance and BDNF levels while downregulating IL-6 levels [20]. Recently, there has been a growing interest in investigating the effects of exercise on irisin and fibroblast growth factor 21 (FGF21). Emerging evidence has shown that irisin plays a role in enhancing synaptic functions in the brain [24]. Since approximately 72% of irisin is produced from muscle secretion, exercise may potentially be an effective method to stimulate the release of irisin, which may in turn improve cognitive function [25]. Previous clinical research demonstrated that a high level of FGF21 was independently associated with cognitive impairment in patients with metabolic syndrome [26], however, exercise interventions could reduce FGF21 levels in obese women and elderly men [27, 28]. Nevertheless, the effects of exercise training on FGF21 levels in individuals with MCI have never been investigated.

Apart from types of exercise, intensity also plays a vital role in the effectiveness of exercise. Previous studies mainly focused on moderate to vigorous exercise. While the promising effects on cognition are evident, some older adults may have limitations or contraindications, such as arthritis, hypertension, and heart disease, which preclude their participation in moderate and high-intensity exercises. Recently, there has been a growing interest in investigating the effects of low-intensity exercise on cognitive function. A limited number of studies found that low-intensity exercise could improve memory [29] and other cognitive functions [30–34] in adults and older adults without cognitive impairment. However, it is unknown whether low-intensity exercise would be beneficial for individuals with MCI. Other common barriers to engaging in regular exercise include a lack of time, schedule conflicts, and transportation constraints, as most exercise training programs are center-based. With those barriers, home-based exercise appears to be a viable alternative. Home-based exercises have been demonstrated to reduce the rate of cognitive decline [35], as well as improve global and specific cognitive function in older adults with and without MCI [36, 37]. Collectively, this study aims to evaluate the effects of home-based, low-intensity, combined physical-cognitive exercise (in the form of an exergame) on cognitive function in individuals with MCI and explores plasma biomarkers potentially underpinning these effects.

## Methods

### Trial design

This is a randomized controlled trial (RCT) with two parallel groups and single-blind outcome assessors. The study protocol conforms to the Consolidated Standards of Reporting Trials (CONSORT) guidelines in which the flow diagram is shown in Fig. 1.

**Fig. 1 Fig1:**
[figure not shown]
Flow diagram of the study procedure

### Study setting

The intervention will take place in a home-based setting. Baseline and post-intervention assessments will be conducted at the Faculty of Associated Medical Sciences, while blood biomarkers will be collected at the Prompt Health Center, Faculty of Associated Medical Sciences, and analyzed at the molecular biology unit of the Cardiac Electrophysiology Research and Training Center, Faculty of Medicine, Chiang Mai University.

### Participants

Participants will be community-dwelling older adults aged 60 years or older. To be eligible for the study participants have to meet the criteria for MCI based on the recent DSM-V criteria [38], comprehend instructions, have adequate vision and hearing, and have physical performance sufficient to exercise at home safely as determined by a score more than 9 of 12 points on short physical performance battery (SPPB) [39]. Exclusion criteria included dementia as determined by a score less than 22 of 30 points on mental state examination T10 (MSET10) [40], depressive symptoms as determined by a score more than 6 of 15 points on Thai geriatric depression scale (TGDS) [41], being diagnosed with other neurological conditions that affect cognition and mobility (e.g., Parkinson’s disease, Stroke, Multiple Sclerosis, and AD), acute or/and chronic disease that could not be controlled (e.g., Arthritis, Asthma, Hypertension, Diabetes mellitus, and Coronary Artery Disease), and exercise regularly (40–50 min/day at least 3 days/week) during the past 3 months [42].

### Recruitment

Participants will be recruited from communities through the distribution of flyers, engagement with community leaders, and utilization of social media. The recruitment process will employ a multimethod approach, incorporating both online and offline advertising targeted towards local communities, health organizations, and companies.

### Randomization and allocation concealment

Participants meeting the eligibility criteria will be randomly allocated to the exercise or control group. Participants will be stratified by age (60–65, 66–69, 70–75, 76–80, or > 80 years), gender (male or female), education level (≤ 12 or > 12 years), and co-morbidity (1–2, or > 2 types) and randomized using a permuted block randomization with varying block size [4, 6, 8] and 1:1 allocation. Randomization will be administered by an individual external to the study using a computer-generated list and concealed within securely sealed, opaque envelopes. All outcome measures will be performed by trained assessors who are blinded to the participant’s group allocation. The researcher will be blinded to the outcome assessments.

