### Sample size calculation

The sample size for the study was determined for the primary outcome measures based on previous studies that examined the effects of Tai Chi which could be considered as combined physical-cognitive exercise at low-to-moderate intensity [48, 49]. The previous findings on memory and executive function yielded effect sizes of 0.40 and 0.38, respectively [49]. Thus, the sample size was estimated using the lowest effect size (i.e., executive function). With 80% power and 5% type I error, a total sample size of 57 (29 per group) will be required to detect change. To accommodate 10% dropout, a total of 64 participants (32 per group) will be enrolled in the study.

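### Forty blocked strata for 64 participants secure only a small part of the intended balance and do not secure 32 per group; the treatment comparison stays unbiased

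*Protocol article*

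**What the plan says.** The Randomization and allocation concealment section of the protocol article names four factors. Age is cut into five bands. The other three have two levels each: gender, schooling (split at 12 years) and the number of co-morbid conditions (one or two against more). Within this stratification, participants are "randomized using a permuted block randomization with varying block size [4, 6, 8] and 1:1 allocation". The list is produced by computer by someone outside the study and held in sealed envelopes.

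The section does not mention minimisation, separate handling of each factor, or a limit on the overall difference between arms. The natural reading is a full cross-classification with its own block sequence in every cell. The bracketed 4, 6, 8 has the form of a citation, but it follows the words on block size and reads as block sizes. Any even block size of 4 or more leads to the same conclusion.

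The Sample size calculation section states that "a total of 64 participants (32 per group) will be enrolled in the study".

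**The concern.** Stratified blocks restrain imbalance fully only in blocks that are completed. When the average cell holds fewer people than half the smallest block, most allocations come from the first one or two places of a block, where the restraint is weak. The leftover imbalances of many cells then add up, both in the arm totals and within each factor.

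Two things are at stake in a trial of this size: how far the four chosen factors are balanced, and how close the arms come to 32 each. There is also a practical burden, since 40 separate envelope sequences must be prepared and used correctly, and most would be opened only a few times or not at all.

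**Working it through.** **Inputs from the protocol article.** Age has 5 levels; gender, education and co-morbidity have 2 each. Blocks are 4, 6 and 8, allocation is 1:1, and N = 64. The enrolment figure reproduces: 57 / (1 − 0.10) = 63.3, rounded up to 64.

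**Cell count.** 5 × 2 × 2 × 2 = 40 cells, and 64 / 40 = 1.6 participants per cell. The article states neither figure. Co-morbidity has no level for people with none, and the Participants section does not require any co-morbidity. If a third level were needed, there would be 5 × 2 × 2 × 3 = 60 cells and 64 / 60 ≈ 1.1 per cell.

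**Assumptions.** The article gives no prevalences, so two sets were assumed:
- equal: every level of a factor equally common;
- skewed: age 0.35/0.25/0.22/0.12/0.06, gender 0.25/0.75, education 0.75 (≤12 years)/0.25, co-morbidity 0.70/0.30.

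Each scheme was simulated over several thousand trials of 64, with block sizes drawn at random.

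**Occupancy under the planned scheme (equal / skewed).** About 32 / 24 cells are occupied. Of these, 90% / 76% hold fewer than 4 people and about 40% hold exactly one. The allocation of a lone person in a cell is a coin toss.

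**Results (equal / skewed).**

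| Scheme | Opened blocks completed | RMS arm difference | 36:28 or worse | Mean imbalance, ≤12 years of education |
|---|---|---|---|---|
| Planned: 40 cells, blocks 4/6/8 | 3% / 13% | 6.5 / 5.5 | 28% / 21% | 3.7 / 3.5 |
| Simple randomisation | – | 8.0 (= √64) | 37–39% | about 4.5 / 5.5 |
| Four cells (age <70 or ≥70, by education), blocks 4/6 | about 78% | about 2.0 | about 0.1% or less | about 1.1 |
| Unstratified blocks 4/6/8 | 94% | about 1.1 | 0% | 3.2 / 2.8 |

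The education figure for simple randomisation is √(2n/π), with n = 32 (equal) and n = 48 (skewed) people at that level.

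**Relative to simple randomisation.** The planned scheme cuts the RMS arm difference by 1 − 6.5/8.0 = 19% to 1 − 5.5/8.0 = 31%. Four cells cut it by 1 − 2.0/8.0 = 75%.

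**Relative to unstratified blocks.** Mean imbalance within age bands is slightly better under the planned scheme (2.3 / 1.9 against 2.6 / 2.4). For the binary factors, averaged over their levels, it is slightly worse (about 3.7 / 3.1 against 3.2 / 2.8).

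**Cost in efficiency.** With arm difference D, the information relative to equal arms is 4·n₁·n₂/N² = 1 − (D/N)².
- For 36:28: 4 × 36 × 28 / 64² = 98.4%.
- On average under the planned scheme: 1 − 6.5²/64² = 99.0% and 1 − 5.5²/64² = 99.3%.

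**The case against.** Four points can be made for the plan.

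- **Part-filled blocks still help.** Two people in the same block of 4 go to opposite arms with probability 2/3, not 1/2. A reader might infer that the scheme amounts to simple randomisation. It does not: the RMS arm difference is 19–31% lower. This stands and limits the claim.
- **The consequence is small.** A reader might infer a biased comparison, an invalid randomisation or a serious loss of power. Nothing in the article supports that. Allocation is still random and concealed within every cell, and the mean efficiency loss is about 1%. This stands too.
- **The analysis absorbs part of any imbalance.** The Statistical analysis section compares baseline with week 12 between groups, so the group-by-time contrast removes stable score differences that go with age or education. It does not remove differences in change over 12 weeks that go with those factors, so the protection is partial.
- **The figure of 32 per group is an enrolment target.** It is not a promise of exact equality, and the article does not say that it relies on stratification to reach it. That is a fair reading. Even so, unstratified blocks of the same sizes would come much closer to it (RMS difference about 1.1 against 5.5–6.5).

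It would also be unfair to count strata whose last block is left open. That is usual in well-designed schemes as well, so the share of opened blocks that are completed is the better measure.

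**Conclusion.** The point holds as a modest weakness in balance. With 40 cells for 64 people, about 3–13% of opened blocks are completed, against about 78% with four strata. A split of 36:28 or worse has a chance of about 21–28%. Imbalance at the lower education level averages about 3.5–3.7 people, against about 1.1 with four strata, and is no better than with blocks that ignore education.

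The cell count follows from the article alone. The other figures rest on the two assumed prevalence sets and on reading the scheme as a full cross-classification; the conclusion is the same under both sets. The stronger readings, that the stratification achieves nothing or that the result would be biased, are not supported. The case for changing the scheme is that better balance is available at little cost.

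**What to change.** **If allocation has not started:** stratify on at most two binary factors. An example is age (<70 or ≥70, which merges the present bands without splitting any) and education (≤12 or >12 years), giving four cells with blocks of 4 and 6. The cost is a new list and a new set of envelopes from the external randomiser, with four sequences in place of 40. The downside is that gender and co-morbidity are then balanced by chance; they can be adjusted for in the analysis.

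**If allocation has started:** keep the existing assignments and adjust for age as a continuous variable, gender, education and co-morbidity. This uses about four degrees of freedom. Entering age as five bands would bring the total to seven (4 + 1 + 1 + 1).

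**Alternative:** minimisation with a random element on all four factors. In simulation with an 80% biased coin, the mean arm difference was about 1.1, against 5.1 / 4.4 for the planned scheme. Each assignment depends on those already made, so it cannot run from envelopes prepared in advance. It is an option only if they are replaced by live allocation.

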### Interventions

#### Exercise group

A low-intensity, combined physical-cognitive exercise will be delivered in the form of an exergame, where the participants move their bodies to interact with the game. The cognitive training, which focuses on memory, attention, and executive function (e.g., anticipation, planning, switching, and inhibition), along with the physical exercise, which focuses on aerobic and balance training, will be incorporated into the game (Table 1). There will be three games with three levels of difficulty (beginner, intermediate, and advanced). Training progression will depend on the participant’s performance. To progress to the next level, participants must achieve a score exceeding 50% at their current level. Prior to training, there will be a familiarization phase to ensure that each participant can safely perform the exercises at home and that the intensity is at a low level. In the training phase, the participants will engage in a 50-minute exercise (7 min warm-up, 36 min of exercise, and 7 min cool-down), 3 times per week for 12 consecutive weeks.

In the familiar phase of exercise, all participants will wear a heart rate monitor watch. The watch will be set at low-intensity ranging between 30 and 39% of each participant’s heart rate reserve (HRR). The Karvonen formula will be used to calculate the HRR (estimated maximal HR − resting HR) and the target HR during exercise (HRR x percentage of training intensity + resting HR) [43]. In addition, they will be subjectively monitored using Borg’s Rating of Perceived Exertion (RPE) scale, with a range of 9–11 out of 20.

**Table 1 Tab1:**
[figure not shown]
Summary of the characteristics of the exercise program

#### Control group

Participants in the control group will not receive any exercise or intervention and be asked to maintain their routine lifestyle. They will be offered the same program as the exercise group after finishing the study.

### Adherence

Exercise adherence will be monitored through the participant’s exercise diary and a record in the exergame program. They will also receive a weekly phone call from the research team to address any questions about the exercise and to provide exercise reminders.

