### Adverse event

Participants will be instructed to immediately report any adverse events occurring during the study. Exercise termination will follow the American College of Sports Medicine (ACSM) standard guideline (e.g., moderate to severe chest pain, severe or unusual shortness of breath, etc.) [44].

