### Assessment and outcome measures

Demographic data of the participants which consisted of age, gender, body mass index (BMI), education level, medical conditions, diet, supplements, lipid profile (high-density lipoprotein cholesterol (HDL), total cholesterol, low-density lipoprotein cholesterol (LDL)), glucose level (Fasting Blood Sugar-FBS) and history of falls in the past year will be obtained. Primary outcome measures will be cognitive performance. Secondary outcomes will be plasma biomarkers via ELISA assays (including BDNF, IL-6, irisin, and FGF21) and physical performance. All assessments will be administered at baseline and post 12-week intervention (Table 2).

**Table 2 Tab2:** Schedule of enrolment, interventions, and measurements for outcome measures

	Study period			
	**Enrollment**	**Allocation**	Post allocation	**Post-intervention**
**Timepoint**	-T1	T0	0–12 weeks	T1 (12 weeks)

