## Discussion

The primary aim of this study is to examine the effects of home-based, low-intensity, combined physical-cognitive exercise on cognitive function of individuals with MCI. To the best of our knowledge, there have not been any intervention trials assessing the impact of home-based, low-intensity exergame on cognitive function in this population. It is anticipated that the game-based exercises will provide enjoyment, while the home-based setting will help overcome common barriers such as schedule conflicts, transportation issues, and family responsibilities, thereby enhancing training adherence. Additionally, plasma biomarkers potentially linking the low-intensity, combined physical-cognitive training to cognitive changes will be explored. The findings of this study might offer an effective intervention program to improve the cognitive and physical performance of older adults with MCI. This program might have important clinical implications as its low-intensity and home-based format would extend accessibility to individuals with MCI who are unable to engage in high-intensity exercise or attend center-based exercise programs. Further, the knowledge gained from the results of the plasma biomarkers would provide a better understanding of the mechanisms underpinning the therapeutic effects of low-intensity, combined physical-cognitive exercise on cognitive function which will have a significant impact on the prevention and management of cognitive impairment.

There are some limitations to this study. First, while the use of a home-based, technology-driven exergame intervention may enhance enjoyment and adherence, it may reduce participation among older adults with low computer or digital literacy. Second, variability in home environments may influence participants’ ability to engage with and benefit from the intervention. To minimize these limitations, a home visit will be conducted prior to the beginning of the home-based intervention to perform an initial home assessment and assist participants with the set up and operation of the exergames. Step-by-step user instructions will be provided for reference. Based on the home assessment, recommendations will be provided to optimize the home setting, promoting safety and a standardized exercise setup. During the home visit, family members or caretakers will be invited to participate, so they can assist the participants throughout the course of the home-based exercise program.

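### Adverse events rest on self-report while only the exercise arm has described staff contact, so reporting may differ by arm, and the trial tests the whole home programme rather than the exercise alone

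*Protocol article*

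**What the plan says.** All references are to the protocol article.

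- **Adherence.** After naming the exercise diary and the exergame record, the section continues: "They will also receive a weekly phone call from the research team". The stated purpose of the call is to answer exercise questions and to remind participants to exercise.
- **Discussion, limitations paragraph.** "a home visit will be conducted prior to the beginning of the home-based intervention". Its purposes include a home assessment and to "assist participants with the set up and operation of the exergames". Family members or caretakers are invited so that they can help throughout the programme.
- **Control group.** "Participants in the control group will not receive any exercise or intervention and be asked to maintain their routine lifestyle". Controls are offered the programme after the study.
- **Adverse event.** "Participants will be instructed to immediately report any adverse events occurring during the study". No scheduled enquiry is described for either arm.
- **Assessment and outcome measures.** "All assessments will be administered at baseline and post 12-week intervention". Table 2 has no adverse-event row. Falls in the past year are asked about with the baseline demographic data.
- **Discussion, aim.** The primary aim is worded as the effect of the home-based, low-intensity combined exercise on cognition. The biomarker work is expected to shed light on mechanisms behind "the therapeutic effects of low-intensity, combined physical-cognitive exercise on cognitive function".

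**The concern.** When events are collected by spontaneous report, the number recorded depends on how often a participant has occasion to mention them. One arm speaks to staff every week; the other has no described contact for 12 weeks. An excess of events in the exercise arm could then partly reflect more conversations, and a real excess could not be told apart from one produced by reporting. This matters because the Background motivates the trial by the needs of older adults whose medical conditions limit harder exercise, and because training takes place at home.

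The same imbalance affects how a cognitive result is read. The exercise arm receives the exergame, a home visit, caregiver involvement and weekly calls, and the control arm receives none of these. A difference at week 12 belongs to that bundle, while the aim names one part of it. The limitations paragraph covers digital literacy and home environment but not the contact imbalance. It offers the home visit and caregiver help as remedies without noting that they add to it.

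**Working it through.** The plan gives no figure on this point to reproduce. The sample size (57, then 64 with dropout) is not affected.

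**Step 1: described contact between baseline and week 12**

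| | Exercise (32) | Control (32) |
|---|---|---|
| Weekly calls (one per week for 12 weeks) | 12 | none described |
| Home visit before training | 1 | none described |
| Caregivers invited to help | yes | none described |
| Instruction to self-report events | yes | yes |
| Scheduled adverse-event enquiry | none described | none described |

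This is 12 + 1 = 13 scheduled contacts per exercise participant, or 32 x 13 = 416 in all. Only the 12 calls (32 x 12 = 384) fall within training. The visit comes before it and cannot pick up training events. That controls get no calls is an inference: the text does not say so outright, but the stated purpose of the calls and the definition of the control condition make it a strong one.

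**Step 2: effect on adverse-event counts**

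Let the true event risk r be the same in both arms. Let p_E and p_C be the probabilities that an event is reported in the exercise and control arms. Then

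apparent risk ratio = (r x p_E) / (r x p_C) = p_E / p_C.

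The documents give neither probability. Assume p_C between 0.30 and 0.50 and p_E between 0.60 and 0.90:

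| | p_C = 0.50 | p_C = 0.30 |
|---|---|---|
| p_E = 0.60 | 0.60/0.50 = 1.2 | 0.60/0.30 = 2.0 |
| p_E = 0.90 | 0.90/0.50 = 1.8 | 0.90/0.30 = 3.0 |

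The range is 1.2 to 3.0. If the calls prompted no extra reports, p_E would equal p_C and the ratio would be 1.

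**Step 3: what the cognitive contrast estimates**

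Exercise arm minus control arm = exergame + familiarisation + home visit + caregiver support + weekly calls, against nothing. Two arms yield one contrast. Randomisation makes it unbiased for the sum, but it cannot divide the sum into parts. Blinded assessors limit bias in scoring. They do not remove effects of attention, expectancy or support on the participant.

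**The case against.** The case on the other side is substantial, and parts of it stand.

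- **Same rule for both arms.** The instruction to report events is addressed to all participants, and the calls are for exercise questions and reminders, not for collecting harms. A reader might infer that harms are captured unequally, or that control events and falls go unrecorded. The text does not support either statement as fact. It supports a risk of unequal reporting.
- **No comparison planned.** Adverse events are neither a primary nor a secondary outcome, and the Statistical analysis section plans no between-arm test of them. The point therefore bears on any descriptive safety table by arm, not on a planned inference.
- **A condensed article.** The full protocol may say more about ascertainment. The point made here is limited to what following the stated rule would produce.
- **A legitimate design.** A passive control is an openly stated choice, and reminders and set-up help are part of delivering a home programme. A reader might infer that the cognitive comparison is biased or invalid. It is not: randomisation protects the programme-versus-nothing contrast.
- **Wording already partly right.** Much of the article's concluding language speaks of a programme, and the Discussion phrase about therapeutic effects sits in a sentence on biomarkers and mechanisms. The aim, however, still names the exercise, and the imbalance is not listed as a limitation.

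What remains is the unequal opportunity to report and the gap between the stated aim and what two such arms can show.

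**Conclusion.** The point holds in limited form. As described, the arms have unequal opportunity to report adverse events and falls: about 12 staff calls per exercise participant during training, against none described for controls. The apparent risk ratio of 1.2 to 3.0 under a true ratio of 1 rests wholly on assumed reporting rates. It illustrates direction and plausible size and is not an estimate for this trial. The cognitive contrast is valid for the whole home programme versus no intervention, but it cannot attribute an effect to the low-intensity exercise apart from contact, attention and caregiver support. The sample size, the randomisation and the primary analysis need no change. This is a cheap improvement rather than a flaw that undermines the trial.

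**What to change.** 1. At the existing week-12 visit, ask every participant in both arms the same structured adverse-event and falls questions covering the past 12 weeks, with caregiver input where available. Ask them after the outcome tests and have existing staff other than the blinded assessors do so, because answers about exercise could reveal the allocation. Base any between-arm adverse-event table on these answers, and list events reported spontaneously or learned from the weekly calls separately.
2. State conclusions as the effect of the whole home programme (exergame, home visit, caregiver support, weekly calls) versus no intervention, and name the contact imbalance among the limitations.

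The cost is a short form, a few minutes per participant and some rewording. Recall over 12 weeks will be imperfect in people with mild cognitive impairment, but both arms are asked the same questions at the same time. The claim also becomes more modest.
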